#### Statistical Power

With the plan to flag 5 patients per week at each referral site, we plan to refer 520 patients per site, generating 1560 total patients referred. A sample size of 520 would lead to 95% Wald CI for referral completion rate by site that is 8.6% in width or smaller. This width provides sufficient precision for our study, considering that (1) a completion rate as small as 10% would be clinically meaningful and (2) we expect to observe a referral completion rate of 50% or higher—in which case, there would be nearly 100% power to reject a referral completion rate of 10% at a significance level of .05 when n=520.

For reference, very few patients were referred from the ED to the mobility and falls clinic prior to our intervention, and the clinic estimates that 80% of their patients referred from other providers visit the clinic. Power can be estimated for detecting a significant intervention effect on fall risk, provided additional covariates are ignored. In this case, a score test for this effect is equivalent to a Cochran-Mantel-Haenszel test of independence in a stratified sample. Such a test has 89.7% power to detect a difference in fall risk of 10% in a stratified sample size of 12 groups (in twelve 8-week periods over 2 years) assuming (1) a significance level of .05, (2) 40 patients receive the intervention and 40 patients do not who have similar risk scores, and (3) an average fall risk of 25%. For reference, our preliminary work predicted a number to treat of about 10 (ie, a fall risk difference of 10%) when setting the risk score threshold so that 5 persons per week receive the intervention (or 40 persons per 8 weeks) and an average fall risk of about 25% for individuals with a fall risk score above or near the fall risk score threshold. We plan on exploratory analysis of pooled data to evaluate the effect of specific covariates on rates of referral; in these cases, power will be lower based on the incidence of specific covariates in the data.

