## Methods

### Setting and Patient Population

This study takes place at 3 EDs, described in Table 1, within a health system in the Midwestern United States. All 3 EDs share an instance of the electronic health record (EHR) developed by Epic, though system configuration (eg, nursing flow sheets and order sets) is not identical at the 3 sites.

**Table 1 table1:** Intervention settings.

ED^a^ site	Type	Intervention implementation date	Approximate annual volume of patients, n	Staffing
ED 1	Academic, level 1 trauma center	February 22, 2022	60,000 (25% geriatric)	Attending group 1, advanced practice providers, residents
ED 2	Community	September 27, 2022	22,000 (28% geriatric)	Attending group 1, advanced practice providers
ED 3	Community	Planned September 2023	65,000 (20% geriatric)	Attending group 2, advanced practice providers

^a^ED: emergency department.

The patient population for our study is individuals aged 65 years or older who present to participating EDs between February 22, 2022, and spring 2026, were discharged, and who had (at the time of ED visit) a primary care provider practicing within the health system in which this study is based. Because the ML-based CDS (ML-CDS) will be implemented in a rolling fashion at different EDs within the system, the start date for data will vary at different study sites. Dates were chosen to have at least two years’ worth of index ED data for each site and an additional 6 months of follow-up ED visits to identify subsequent falls.

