## Results

As of April 30, 2023, the CDS tool has been implemented at 2 of the 3 sites. Providers at ED 1 have written 303 referral orders for 260 unique patients, or 5 referrals per week on average, which is our goal. ED 2, the community ED, has not been live with the ML-CDS as long, and providers have written 91 referral orders for 86 different patients, or just over 3 referrals per week. Both EDs refer roughly 30% of patient encounters the algorithm identifies: 303 referrals for 1007 patients flagged at ED 1 and 91 referrals for 319 patients flagged at ED 2. The patient populations between these 2 EDs have substantial overlap, and 6 patients have received referrals from both EDs. After conversations with the mobility and falls clinic, we do not see repeat referrals as a problem unless the patient has already completed 1 of the referrals, so our ML-CDS tool was updated to exclude patients with a completed or scheduled appointment at the mobility and falls clinic. Notably, the patient uptake of the final intervention is about 15% of patients referred—45 patients of 339 unique patients; 1 patient was seen at and referred by both ED 1 and 2—which is less than the 80% that the clinic estimates for other referral sources. While not surprising that uptake would be lower from ED provider referrals than from primary care provider referrals, this conversion rate is lower than we anticipated, and we have taken steps to improve messaging, patient follow-up, and providers’ ability to talk to patients about the program, and we have taken other steps that have shown some improvement appointment conversion in recent months. Additionally, waning concerns about COVID-19 have seemed to increase patients’ willingness to consider completing the referral.

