### Significance of Principal Findings

Previous work with ML-CDS tools has focused on their implementation in a specific context [33] or on the predictive performance [34] of the underlying algorithm. Our unique data set will include information about patient’s health history (eg, health care use) prior to the ED index visit, referral completion, and subsequent ED return visits for falls (either in the system or from Medicare claims), providing a more complete picture of a given patient’s trajectory than most studies. We will use this unique data set to track not just ML-CDS performance in the context of its implementation, but in the context of larger patient health outcomes, which, to our knowledge, has not been done for this kind of long-term, preventative ML-CDS system. Similarly, the multisite implementation plan will demonstrate applicability to a broad population and the possibility to adapt the intervention to other EDs and achieve similar results.

Our statistical methodology (a regression discontinuity design) allows for an intent-to-treat causal inference about the impact flagging high-risk patients can have on patients’ future falls. Conversations with patients about the referral, even if a referral is not written, could have impacts on patients’ risk awareness and compliance with physical therapy, so ML-CDS flagging is the correct epidemiologic exposure to assess with respect to the outcomes of completed mobility and falls visits or return ED visits for falls. A staggered implementation strategy allows for the identification of secular trends that could affect causal association and mitigation as necessary.

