### Limitations

To achieve the desired number of clinic referrals per week, the falls risk threshold for the CDS identification will be changed over time. Because regression discontinuity designs typically assume a static threshold for analysis, we will need to approach the regression discontinuity analysis carefully and with sufficient sensitivity analyses to ensure that these threshold changes do not compromise the findings. Simulation studies will be conducted to ensure the assumptions of regression discontinuity analysis are met.

Clinically, our assumptions about the effectiveness of the mobility and falls clinic intervention are based on PROFET (Prevention of Falls in the Elderly Trial) [13], which specifically evaluated patients referred from the ED. The intervention is based on evidence from a randomized clinical trial, but the magnitude of the effect may be different in our patient population—for example, due to endogenous factors like demographic composition of the community or exogenous factors related to changes in care patterns during the COVID-19 pandemic. In addition to methodological concerns, there are some pragmatic limitations. First, the intervention was implemented during the COVID-19 pandemic. During the study period and community, there were—and could continue to be—multiple waves of elevated SARS-CoV-2 infections and case counts that may dissuade some patients from scheduling an appointment at the mobility and falls clinic. Similarly, in order to maximize patient impact and to study the human factors inputs to this system, efforts were made to increase referral rates and referral completion with providers and patients. While these efforts will likely increase the statistical power over time, it is also likely that there will be secular effects in the imperfect compliance with referral rates and referral completion rates that are present in the data as a result of these efforts.

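### The falls power rests on 5 flagged patients per week per site, but 5 per week is the referral target and the live sites flag about 16 and 10 encounters per week; its inputs are not shown to fit the patients compared, and 89.7% does not reproduce.

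*Protocol article*

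**What the plan says.** In the protocol article, Statistical Power begins "With the plan to flag 5 patients per week at each referral site" and goes straight on to 520 patients referred per site. For falls it states 89.7% power for a 10-point risk difference, using a Cochran-Mantel-Haenszel test in 12 periods of 8 weeks, with 40 exposed and 40 unexposed patients per period and an average risk of 25%. The difference and the average risk are attributed to preliminary work "when setting the risk score threshold so that 5 persons per week receive the intervention".

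Other sections describe a different quantity:

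- The section on the secondary outcome says the intervention goes to patients scoring above the threshold, and compares those identified as high risk with those who were not.
- Significance of Principal Findings states that "ML-CDS flagging is the correct epidemiologic exposure to assess".
- Results calls 5 referrals per week the goal and reports "303 referrals for 1007 patients flagged at ED 1 and 91 referrals for 319 patients flagged at ED 2".
- Limitations says that "the falls risk threshold for the CDS identification will be changed over time", so as to reach the desired number of clinic referrals.

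**The concern.** A risk-score threshold decides who is flagged; the provider then decides who is referred. If about three in ten flagged encounters are referred, a threshold that yields 5 referrals per week must flag far more than 5. The power paragraph uses one number for both.

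This reaches the falls power because three of its inputs (group size, average risk and absolute difference) are tied to a threshold passing 5 per week. If the thresholds in force pass two to three times as many, those inputs may describe a different group from the one in the analysis. At stake is whether the stated 89.7% tells the reader anything about the falls comparison that will be made.

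**Working it through.** **1. The plan's own figure.** Inputs from Statistical Power: 12 periods × 40 = 480 per arm; average risk 25% with a 10-point difference, so 30% versus 20%; alpha .05. Sidedness is not stated, and two-sided is assumed. With equal arms and constant risk across periods, the test is close to a two-proportion comparison:

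power = Φ[(d − 1.96·SE0) / SE1], where d = p1 − p2, SE0 = √(2·p̄(1 − p̄)/n) and SE1 = √((p1(1 − p1) + p2(1 − p2))/n).

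- SE0 = √(2 × 0.25 × 0.75/480) = 0.02795
- SE1 = √((0.21 + 0.16)/480) = 0.02776
- (0.10 − 1.96 × 0.02795)/0.02776 = 1.63, so power = **94.8%**

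Simulating the stratified test itself (12 strata of 40 versus 40, 50,000 runs) gives 95.0%, or 94.1% with a continuity correction. Other readings of the risks also miss 89.7%: 25% versus 15% gives 97.3%, and 35% versus 25% gives 92.4%. A 9-point difference around 25% does give 89.7%, but the text says 10.

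**2. Flag and referral rates.** Start dates come from Table 1, and counts to 30 April 2023 from Results.

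| | ED 1 | ED 2 |
|---|---|---|
| Weeks live | 432 days/7 = 61.7 | 215 days/7 = 30.7 |
| Flagged per week | 1007/61.7 = 16.3 | 319/30.7 = 10.4 |
| Flagged per 8 weeks | 131 | 83 |
| Ratio to the 5 per week assumed | 3.3 | 2.1 |
| Referral orders per week | 303/61.7 = 4.9 | 91/30.7 = 3.0 |
| Orders per flag | 30% | 29% |

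The Abstract describes the total of 1326 (1007 + 319) as encounters, so these rates are upper bounds for unique patients. Scaling by unique patients per referral order (260/303 and 86/91, which is an assumption for flags) leaves about 14.0 and 9.8 per week. The rates also average over a moving threshold.

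**3. Illustration of what could change.** The article gives no fall risk at the thresholds in force, so the risks below are assumptions, apart from the plan's 25%. The plan's relative effect is kept (difference = 0.4 × average risk), with the formula of step 1. Observed counts over 96 weeks are about 1,560 (ED 1) and 996 (ED 2) per arm. They assume that every flag is a separate patient inside the analysis band, with equally many comparators.

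| Average risk | Difference | 480 per arm | ED 1 count | ED 2 count |
|---|---|---|---|---|
| 25% (plan) | 10 points | 94.8% | >99.9% | 99.9% |
| 20% | 8 points | 87% | >99.9% | 99.4% |
| 15% | 6 points | 74% | 99.7% | 96% |
| 10% | 4 points | 54% | 96% | 85% |

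The like-for-like baseline for this table is 94.8%, not 89.7%. All values ignore adjustment for the risk score.

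**The case against.** The strongest reply is that receiving the intervention could mean being referred, in which case ED 1 is on plan. That does not hold. ED 2 would still be at 3 per week, and the design sections define exposure by the threshold and by flagging.

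A second reply is that Limitations already discloses the moving threshold and promises sensitivity analyses and simulations. It does, but for the validity of the discontinuity analysis; the power inputs are not revisited. Falls are also the secondary outcome, which limits the weight of the point.

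Three stronger readings are tempting and are not supported:

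- *The falls comparison is underpowered.* A lower cut-off with lower risk is a plausible consequence of more flagging, but it is an inference. The article gives no threshold values, and the algorithm is retrained for each site. Even if risk is lower, the larger counts work the other way: three of the four count-based values at 15% and 10% risk exceed 89.7%.
- *One fall risk cannot hold at all three sites.* Geriatric volumes from Table 1 do differ (60,000 × 25% = 15,000; 22,000 × 28% = 6,160; 65,000 × 20% = 13,000). The eligible population, however, is discharged patients with an in-system primary care provider, and its size is not given.
- *The planned threshold is never in use.* The observed rates are averages over changing thresholds, and ED 3 was not live.

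The analysis band may also hold only some of the flagged patients, so 40 per period could still occur. The 25% and 10-point inputs would remain tied to a threshold passing 5 per week.

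**Conclusion.** The point holds in a limited form. The power paragraph treats flagging and referral as the same event, and the article's own counts show flagging at 3.3 times (ED 1) and 2.1 times (ED 2) the assumed rate, or somewhat less in unique patients. The 40 per period, 25% risk and 10-point difference are therefore not shown to describe the patients who will be compared. The net direction of the effect on power is not determined by the article.

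Separately, the stated inputs give about 95% rather than 89.7%, assuming a two-sided test and constant risk across periods. That discrepancy is on the cautious side, but it means the printed figure cannot be traced to its printed inputs. The flag rates rest on the article's dates and counts; the power values at 20%, 15% and 10% risk rest on assumed risks and a constant relative effect.

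**What to change.** Reconcile the 5-per-week flag rate in Statistical Power with the referral target in Results and Limitations, and say which population the 25% risk and 10-point difference describe.

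For each live site, take from the EHR data the number of unique flagged patients and comparators per period within the analysis band, and the mean predicted risk near the threshold in force. Recompute the falls power per site from these, with the effect scaled to that risk and the test's sidedness stated, and replace the single 89.7%. For ED 3, label the inputs as assumptions until it is live.

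The cost is a query of data the study already plans to retrieve and one rewritten paragraph. The stated power will change.

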#### Secondary Outcome: Return Visits to ED for a Fall

Although the intervention is not randomized, our study has a quasi-experimental design known as a sharp regression discontinuity with regards to intent-to-treat, since the intervention is administered to patients whose risk score falls above some threshold. This design allows for causal inference, provided that differences in outcomes for patients with similar risk scores can be attributed to the intervention (formally, expected potential outcomes are continuous in risk score). This occurs when patients are not manipulating their assignment to the intervention. Assuming this holds, we will primarily analyze only those patients whose risk scores fall within a band around the risk score threshold. Additionally, patients will be stratified by ED arrival date to account for changes to this threshold to be aligned with a sharp research continuity design. A conditional logistic regression model will be built to describe 6-month fall risk at each site as a function of the intervention, patient demographics, and risk score. The odds ratio of a return visit for fall and the 95% CI will be estimated by comparing those identified as high risk by the ML-CDS algorithm and those who were not but had a similar risk profile. Sensitivity analyses will be performed to examine the influence of bandwidth choice and key assumptions (ie, continuity of potential outcomes and linearity in risk score) on estimates. A secondary analysis will be to investigate the effect of covariates on completed referrals and falls using a stratified Cox proportional hazards model for time-to-fall events (right-censored by follow-up time).

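### The 89.7% power for the fall outcome belongs to a test without the risk score, whereas the planned regression discontinuity model includes it, so the figure is not the power of the planned analysis

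*Protocol article*

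**What the plan says.** In the protocol article, Secondary Outcome: Return Visits to ED for a Fall, the flag is assigned when the risk score exceeds a threshold. The analysis is restricted to a band: "we will primarily analyze only those patients whose risk scores fall within a band around the risk score threshold". Within arrival-date strata, a conditional logistic model describes "6-month fall risk at each site as a function of the intervention, patient demographics, and risk score". The same section lists linearity in the risk score among the assumptions to be examined in sensitivity analyses.

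The Statistical Power section introduces its fall calculation with a condition: "Power can be estimated for detecting a significant intervention effect on fall risk, provided additional covariates are ignored". It then equates the score test with a CMH test and states: "Such a test has 89.7% power to detect a difference in fall risk of 10% in a stratified sample size of 12 groups". The inputs are twelve 8-week periods, "a significance level of .05", "40 patients receive the intervention and 40 patients do not who have similar risk scores" in each period, and "an average fall risk of 25"%. The 40 per period is derived from 5 persons per week. No power is given for the model that contains the risk score.

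**The concern.** In a randomized trial, leaving covariates out of a power calculation is usually harmless. Here the flag is a deterministic function of the risk score, so the score is the running variable on which the causal comparison rests, not an optional covariate. Flag and score are strongly correlated inside any band, and adjusting for the score costs precision. A calculation that ignores it therefore overstates the power obtained from a given number of patients.

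At stake is how a null site-level result on falls will be read. With 89.7% on record, it would be taken as evidence against a 10-point effect from a study powered at about 90%, which the planned model may not be.

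**Working it through.** **Inputs.** From Statistical Power: 12 strata of 40 versus 40, so n = 480 per group; a risk difference of 10 points; average risk 25%, read as 20% versus 30%; significance level .05. Sidedness is not stated; two-sided is assumed, since the plan reports 95% CIs.

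**1. The stated figure.** SE = √(2 × 0.25 × 0.75 / 480) = 0.02795. z = 0.10 / 0.02795 = 3.578. Power = Φ(3.578 − 1.960) = 94.7% (94.8% with the unpooled variance under the alternative). Simulating the CMH test gave 94.9%, or 94.1% with continuity correction. Variants near 89.7% each change a stated input:
- 30% versus 40% gives 90.2% (89.0% corrected), but the average risk is then 35%.
- Significance level .025 with correction gives 89.8%.
- Ten strata instead of twelve (400 per group) give 90.7% (89.2% corrected).

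So 89.7% is not reproduced. It is about 4–5 points below what its inputs give.

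**2. Cost of including the score.** The variance of the flag effect is multiplied by VIF = 1/(1 − ρ²), where ρ is the flag–score correlation in the band. The article gives no score distribution, so these are assumptions, each with half the patients on either side of the threshold:
- Uniform on (−1, 1): covariance 1/4, flag variance 1/4, score variance 1/3; ρ² = (1/16)/(1/12) = 0.75; VIF = 4.
- Normal centred on the threshold: ρ² = 2/π = 0.637; VIF = 2.75.
- Skewed (exponential tail), common slope: ρ² = (ln 2)² = 0.480; VIF = 1.92, taken as 1.9.

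**3. Power of a model with a linear score.** Power = Φ(z/√VIF − 1.960). The last column starts from the z implied by 89.7%: 1.265 + 1.960 = 3.225.

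| Score in band | VIF | From z = 3.578 | From z = 3.225 |
|---|---|---|---|
| Uniform | 4 | 43% | 36% |
| Normal | 2.75 | 58% | 49% |
| Skewed | 1.9 | 74% | 65% |

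Simulated logistic models with stratum effects and a linear score gave 41–42% (uniform), 58% (normal) and 68–70% (skewed). For the skewed score, separate slopes on each side raise VIF to 3.4, which gives 49% (42% from z = 3.225). Power drops below 80% once VIF exceeds (3.578/2.802)² = 1.63, or (3.225/2.802)² = 1.32 from the stated figure. The difference detectable with 89.7% power is 3.225 × √VIF × 0.02795: about 12 points (VIF 1.9), 15 (2.75) or 18 (4).

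**4. Is 480 flagged per site the right number?** The Results give 1007 flags at ED 1 from February 22, 2022 to April 30, 2023 (61.7 weeks, 16.3 per week) and 319 at ED 2 from September 27, 2022 (30.7 weeks, 10.4 per week). The 5 per week is ED 1's referral rate (303/61.7 = 4.9), whereas the exposure in this analysis is the flag. Over 104 weeks these rates give about 1,700 and 1,080 flags. The share inside the band is unknown. Assuming equal numbers on both sides, 20% versus 30%:

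| Flagged in band | VIF 4 | VIF 2.75 | VIF 1.9 |
|---|---|---|---|
| 1,700 (ED 1, all) | 92% | 98% | >99% |
| 850 (ED 1, half) | 66% | 82% | 93% |
| 1,080 (ED 2, all) | 77% | 90% | 97% |
| 540 (ED 2, half) | 48% | 63% | 79% |
| 240 (half of the stated 480) | 24% | 33% | 45% |

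The counts are encounters, not unique patients, so the effective numbers are somewhat smaller.

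**The case against.** The strongest reply is that the simplification is disclosed. The 89.7% is conditional on ignoring covariates, and the comparators are described as having similar risk scores. In a narrow enough band the score might matter little. The disclosure deserves credit, but it does not settle the matter: the planned model contains the score, and linearity in it is a named assumption. The only warning that power will be lower concerns exploratory pooled analyses of referral rates. The simulation studies promised under Limitations address the design's assumptions, not power.

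Three other points stand in part. Falls are the secondary outcome, and the precision calculation for referral completion is untouched. Pooling three sites of 480 versus 480 would give about 87–99% under the same distributions, but the model is planned at each site. The failure of 89.7% to reproduce runs the other way, since it understates the power of the test it describes.

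A reader might infer that true power is 43–58% per site, or that the study is underpowered for falls. The article does not support either. That range needs uniform or normal scores and exactly 480 flagged patients in the band, and the observed flag rates could put power well above it. A reader might also infer that the fall estimate will be biased because the score is omitted. It is omitted only from the power calculation, not from the planned analysis.

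**Conclusion.** Wrong as written, and should be fixed. The 89.7% is not the power of the planned per-site model, and it does not follow from its own inputs, which give about 95% (about 94% with continuity correction). On the stated 480 versus 480, a model with a linear risk score has about 43–74% power for 20% versus 30%, or about 36–65% if scaled from 89.7%. These ranges rest on a two-sided .05 level, an even split at the threshold and an assumed score distribution (uniform, normal or skewed); demographic terms are not counted. The direction is firm for the stated sample size: every distribution tried falls below 80%. The actual power is not known, because the assumed 5 flags per week conflicts with the Results and the number inside the band is not stated.

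**What to change.** Replace 89.7% with the power, or the detectable difference, of the planned model. Compute it by simulation from the existing ED 1 and ED 2 score distributions, the observed flag counts, the chosen bandwidth and the changing thresholds. State the expected number of patients in the band on each side of the threshold, and say whether 5 per week means flags or referrals. Remove the statement that power can be estimated with the risk score ignored.

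The cost is one rewritten paragraph and a modest simulation, with no extra patients or data. The downside is that the stated figure may become less favourable.

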## Abstract

**Background:**

Emergency department (ED) providers are important collaborators in preventing falls for older adults because they are often the first health care providers to see a patient after a fall and because at-home falls are often preceded by previous ED visits. Previous work has shown that ED referrals to falls interventions can reduce the risk of an at-home fall by 38%. Screening patients at risk for a fall can be time-consuming and difficult to implement in the ED setting. Machine learning (ML) and clinical decision support (CDS) offer the potential of automating the screening process. However, it remains unclear whether automation of screening and referrals can reduce the risk of future falls among older patients.

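### The 89.7% power for the fall comparison assumes an undiluted 10-point difference, although the comparison is intent-to-treat on a flag that leads to referral about 30% of the time

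*Protocol article*

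**What the plan says.** All references are to the protocol article.

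- **Statistical Power.** "Such a test has 89.7% power to detect a difference in fall risk of 10% in a stratified sample size of 12 groups", with strata of eight weeks over two years. Each stratum is taken to hold patients such that "40 patients receive the intervention and 40 patients do not who have similar risk scores", with "an average fall risk of 25" percent. The 10 points is justified by "our preliminary work predicted a number to treat of about 10 (ie, a fall risk difference of 10" percent), for a threshold at which five people a week receive the intervention. The same section plans to flag five patients a week per site and to refer 520 per site. Five a week for 104 weeks is 520, so flagged, referred and treated patients are counted as one group.
- **Secondary Outcome: Return Visits to ED for a Fall.** The odds ratio compares patients the algorithm identified as high risk with patients of similar score whom it did not. The design is described as sharp with regard to intent-to-treat.
- **Significance of Principal Findings.** The design "allows for an intent-to-treat causal inference about the impact flagging high-risk patients can have" on later falls. Flagging is named as the exposure for both outcomes.
- **Results (to 30 April 2023).** "303 referrals for 1007 patients flagged at ED 1 and 91 referrals for 319 patients flagged at ED 2". Of 339 unique referred patients, 45 took up the clinic. The Abstract describes these 45 as having scheduled an appointment.
- **Background and Limitations.** "ED referrals to falls interventions can reduce the risk of an at-home fall by 38" percent. Limitations says the assumed clinic effect rests on the cited randomized trial of patients referred from the ED. It acknowledges imperfect compliance but does not return to the power figure.

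**The concern.** An intent-to-treat contrast on the flag averages over everyone flagged, including those never referred and those referred who never attend. An effect that comes through referral or through the clinic is diluted by those shares. The power section uses 10 points for the flag contrast as if no dilution occurred, while the Results of the same article show that most flagged patients do not move to the next step.

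What is at stake is how the fall result can be read. This is a secondary outcome, but it carries the article's causal claim. If the real contrast is a few points or less, the comparison would most often be inconclusive even if the clinic works as assumed. A printed power near 90% would then misdescribe how much such a result can tell.

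**Working it through.** **Inputs.** From Statistical Power: 12 strata of 40 against 40, so 480 per arm; average risk 25%; significance level .05, taken as two-sided because the article does not say. From Results: flags 1007 and 319; referral orders 303 and 91; uptake 45 of 339. The hoped-for completion rate of 50% or more is also from Statistical Power.

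**Step 1: the plan's own figure.** With equal strata and a common risk, the Cochran-Mantel-Haenszel test behaves as a two-proportion test with 480 per arm. For 30% against 20%:

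- null SE = √(2 × 0.25 × 0.75 / 480) = 0.02795
- alternative SE = √((0.30 × 0.70 + 0.20 × 0.80) / 480) = 0.02776
- power = Φ[(0.10 − 1.96 × 0.02795) / 0.02776] = Φ(1.63) = 94.8%

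A simulation of the stratified test also gave 94.8%. The printed 89.7% is therefore not reproduced from its literal inputs. A 9-point difference centred on 25% gives 89.7%. The printed figure is the more cautious one, and this discrepancy is separate from the present point.

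**Step 2: uptake.**

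- Referred among flagged: 303/1007 = 30.1%; 91/319 = 28.5%; combined 394/1326 = 29.7%.
- Scheduled among referred: 45/339 = 13.3% (the article prints about 15%).
- Scheduled among flagged: 0.30 × 0.133 = 4.0%. Dividing directly, 45/1326 = 3.4%; with the printed 15%, 0.297 × 0.15 = 4.5%.

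**Step 3: diluted difference and power.** Difference = 10 points × the share reached, assuming the flag does nothing by itself. Power is two-sided, 480 per arm, centred on 25%.

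| What the 10 points applies to | Share of flagged reached | Difference (points) | Power |
|---|---|---|---|
| Per flag (as printed) | 100% | 10 | 94.8% (printed 89.7%) |
| Per visit, all referred, 80% complete | 80% | 8 | 82% |
| Per visit, all referred, 50% complete | 50% | 5 | 43% |
| Per referral, 30% referred | 30% | 3.0 | 19% |
| Per visit, 30% referred, 50% complete | 15% | 1.5 | 8% |
| Per visit, 30% referred, 13.3% take up | 4% | 0.4 | 5% |

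At 3 points, 0.030 / 0.02795 = 1.07, so power is Φ(1.07 − 1.96) plus a negligible other tail, or 19%. Reaching 89.7% at 3 points would need about 4,331 per arm. The 80% row uses the clinic's estimate for its other referral sources.

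**Step 4: more flags than planned.** From 22 February 2022 to 30 April 2023 is 61.7 weeks, so ED 1 flags 1007/61.7 = 16.3 a week, not 5. Over the 96 weeks of the power calculation that is about 1,566 flagged. If all lay within the band and were matched by as many controls, power would be 49% at 3 points and 6% at 0.4 points. Over 104 weeks (about 1,697 a side) it would be 52% and 6%. The planned restriction to a band around the threshold would lower these. Pooling three sites at 480 per arm each (1,440 per arm) gives 46% at 3 points.

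**The case against.** The strongest reply is that the article never says the 10 points is a clinic effect at full uptake. It attributes the figure to preliminary work whose derivation is not shown, and it describes the 38% reduction as an effect of ED referral. If the 10 points is per referral, only the 30% step applies. The 1.5- and 0.4-point rows then fall away and 3 points is the relevant figure. This stands, so those rows hold only under a per-visit reading.

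A reader might also infer that 10 points requires the full effect in every flagged patient, because 0.38 × 25% = 9.5 points. That does not follow. The multiplication treats 25% as the untreated risk, whereas the power section calls it an average. If 25% is the mean of both arms, a 38% reduction is about 30.9% against 19.1%, or 11.7 points, and 10 points is about 85% of it. Even so, 30% of 11.7 is 3.5 points, with about 24% power.

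Third, Hypothesis and Expected Findings and Significance of Principal Findings both expect benefit from conversations with flagged patients who are not referred. That is why the flag was chosen as the exposure. No size is given, so the diluted figures cannot be called the expected effect without the stated assumption that the flag alone does nothing. In the other direction, if referred patients gain 10 points each, the unreferred 70% would need to gain 10 points each as well for the flag contrast to reach 10.

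Finally, the rates are interim, ED 3 had not started, and steps to raise uptake are reported. The shares also mix encounters with unique patients. All of this is true, and it argues for a range rather than for leaving one undiluted figure in place.

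**Conclusion.** The stated power does not apply to the contrast the article plans to estimate. It rests on an undiluted 10 points, while the exposure is the flag and the article's own data show about 30% of flags referred and about 13 to 15% of referred patients scheduling. Under a per-referral reading with no effect of the flag alone, the difference is about 3 points and power about 19% at 480 per arm. It is about 50% if the higher flag rate at ED 1 continued and every flagged patient lay in the band. Under a per-visit reading, power is 8% at 50% completion and 5% at reported uptake. Even universal referral with 50% completion gives 5 points and 43%.

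A reader might go further and conclude that the true difference will lie between 0.4 and 3 points, or that the article would report a null as proof of no benefit. The documents support neither. The range depends on the assumptions above. The Outcomes section says only what the fall outcome is meant to reflect, and an odds ratio with 95% CI is already planned. The primary outcome's precision is unaffected. This is a misstated property of a secondary analysis.

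**What to change.** In Statistical Power:

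1. State whether the 10 points is an effect per flag, per referral or per completed visit, and how the preliminary work obtained it.
2. Count flagged, referred and attending patients separately, instead of as one group of five a week.
3. Replace the single 89.7% with power for the intent-to-treat difference over a stated range of referral and completion rates. The range should include the interim rates and the hoped-for 50% completion.
4. State the assumption made about any effect of the flag without referral, and show power with that effect at zero and at one or more plausible sizes.
5. Base the per-arm number on patients expected within the band at the observed flag rate.

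The cost is wording and a short recalculation. Data collection is set by calendar dates, so neither the sample nor the planned analysis has to change. The stated power for this secondary outcome will fall, by how much depending on items 1 and 4.
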